### Outcomes {12}

The primary outcome is time to first hospitalisation or death from all causes during 1 year after randomisation in people with COPD (at 1 year, assessed using nationwide registries).

Secondary outcomes are as follows:Time to first all-cause hospitalisation or all-cause death in people with ILD (at 1 year after randomisation, assessed using nationwide registries).Rate of hospitalisations or death from all causes (at 1 year).Hospitalisation rate from all causes (1-year and long-term).Hospitalisation rate from respiratory disease (1-year and long-term).Hospitalisation rate from cardiovascular disease (1-year and long-term).Number of hospitalised days (all-cause/respiratory disease/cardiovascular disease) (at 1 year and long-term).Number of admissions to intensive care unit (ICU) (at 1 year and long-term).Number of days in ICU care (at 1 year and long-term).The mortality rate from all causes (at 1 year and long-term).The mortality rate from respiratory disease (at 1 year and long term). The mortality rate from cardiovascular disease (at 1 year and long-term).Time to first exacerbation after randomisation, defined as time to first dispensed antibiotics and/or oral corticosteroids, emergency department visit, or hospitalisation for exacerbation (at 1 year).Number of exacerbations of all severity (at 1 year).Incidence of cardiovascular disease (at 1 year and long-term).Need for home mechanical ventilation (at 1 year and long-term).Rate of LFOT withdrawal (at 1 year and long-term).Safety and tolerability (adverse events at 3 and 12 months).Cost-effectiveness (at 1 year and long-term).HRQL (at 3 and 12 months).Symptoms (dyspnea, cough, phlegm, upper airway symptoms, fatigue, including nighttime symptoms, sleep) (at 3 and 12 months).Factors associated with the net clinical benefit of the HFOT, including the daily usage time.Patients’ perceptions of oxygen therapy and related factors.Adverse events as safety endpoints.

The secondary outcomes will be evaluated in the following populations: (1) people with COPD; (2) people with ILD; and (3) all people. All analyses will be performed primarily by randomised treatment group (intention to treat; ITT), and secondarily by treatment used (per protocol; PP).

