### Sample size {14}

The sample size will be 270 randomised people with COPD and with data on the primary outcome. This sample size was determined to provide 80% power to detect a clinically meaningful between-group difference in the primary outcome (time to first hospitalisation or death from all causes during 1 year) of hazard ratio 0.67 in people with COPD, using a two-sided test, assuming equal allocation between the treatment groups, a 1-year rate of the primary outcome of 0.74 in the target population in the Swedevox registry; and a false positive rate (alpha) of 0.05 [33].

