## Statistical methods

### Statistical methods for primary and secondary outcomes {20a}

A detailed statistical analysis plan (SAP) will be established and published in collaboration with a biostatistician before the lock of the database for the primary analysis and before performing each secondary analysis.

The population for efficacy analyses is defined as all randomised people who did not withdraw their consent to be included in the outcome analyses (ITT population). The population for safety analyses is defined as all randomised people who started their randomised treatment (safety population). All analyses will be performed primarily by randomised treatment group (ITT) and secondarily by treatment used (PP).

Data will be summarised using mean with standard deviation and median with range and interquartile range for continuous variables with normal and skewed distributions, respectively. Categorical variables will be expressed as frequencies and percentages. Differences between groups will be analysed using Student’s *t*-tests (for normally distributed continuous outcomes), chi2 tests (for dichotomous outcomes), and Wilcoxon’s rank sum test (for ordinal and non-normally distributed data).

Outcomes will be compared between the treatment groups using multivariable regression models, expressed as point estimates with 95% confidence intervals. The primary outcome will be analysed using Cox proportional-hazards regression. Secondary outcomes will be analysed using appropriate statistical methods: logistic regression for categorical outcomes, Cox regression for standard survival analysis, Fine–Gray regression for competing risk scenarios, and linear regression for continuous outcomes, ensuring robust and context-appropriate analysis. Mixed regression models with random effects will be used to analyse outcomes measured in the same individual at several time points to account for repeated measurements. The outcome analyses will be adjusted for age and sex, the stratification variables, number of hospitalisations during the 12 months before baseline, and time from starting LFOT in Swedevox. Statistical significance will be defined as a two-sided *p*-value < 0.05.

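### The named secondary-outcome models take no account of time at risk in the count and day outcomes, so an arm with more early deaths can look better on them

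*Protocol article*

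**What the plan says.** The list under Outcomes {12} includes several totals per participant: "Number of hospitalised days (all-cause/respiratory disease/cardiovascular disease) (at 1 year and long-term"), "Number of days in ICU care (at 1 year and long-term"), the number of ICU admissions and the number of exacerbations. It also includes outcomes worded as rates: all-cause, respiratory and cardiovascular hospitalisation, and a composite of hospitalisation or death. Most are to be reported both at 1 year and long-term; exacerbations and the composite rate are for 1 year only. No rule is given for how death enters the totals.

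Statistical methods {20a} pairs types of outcome with models: "logistic regression for categorical outcomes, Cox regression for standard survival analysis, Fine–Gray regression for competing risk scenarios, and linear regression for continuous outcomes". It adds mixed models for outcomes measured at several time points and, for unadjusted comparisons, t, chi-square and Wilcoxon tests. It names no Poisson, negative binomial or recurrent-event model and no person-time term. A detailed SAP is promised before database lock and before each secondary analysis.

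**The concern.** Under the stated pairing, a count or a number of days is either a continuous outcome, which goes to linear regression, or a non-normal one, which goes to a rank test. Neither knows how long the participant was alive to accumulate events. Someone who dies on day 10 can have at most 10 hospital days and so scores better than a survivor with 20. Fine–Gray does not help, because it treats death as a competing risk for the time to an event, not for a total.

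Death is part of the primary outcome, so the trial allows that HFOT may change survival. If it does, exposure differs between arms. The arm that lives longer collects more admissions and days, which could understate a benefit or make a harm less visible on these outcomes.

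**Working it through.** **The plan's own figure.** Sample size {14} states: "The sample size will be 270 randomised people with COPD and with data on the primary outcome", for "80% power to detect a clinically meaningful between-group difference in the primary outcome", with "hazard ratio 0.67 in people with COPD", two-sided alpha 0.05, equal allocation and a 1-year primary-event proportion of 0.74.
- Schoenfeld: 4 × (1.960 + 0.842)² / (ln 0.67)² = 196 events; 196 / 0.74 = 265 people.
- Freedman: (1.960 + 0.842)² × (1.67 / 0.33)² = 202 events after rounding up; 202 / 0.74 = 273 people.

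Both are close to 270. The sample size is sound on its stated inputs, and this point does not touch it.

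**Inputs for the count and day outcomes.** The article gives no 1-year mortality, so the following are assumptions:
- LFOT 1-year mortality m of 15%, 20%, 30% or 40%.
- Exponential survival with hazard λ = −ln(1 − m).
- A mortality hazard ratio of 0.67, borrowed from the composite only to have a scale.
- The same event rate while alive in both arms.

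**Formula.** Mean time alive over T years is (1 − exp(−λT)) / λ. With equal event rates while alive, the ratio of mean counts equals the ratio of mean times alive.

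**Results.** The article does not say how long the long-term follow-up is; 3 years with constant hazards is assumed here.

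| LFOT mortality | HFOT mortality | Mean years alive in year 1, LFOT / HFOT | Count ratio HFOT/LFOT, 1 year | Count ratio, 3 years |
|---|---|---|---|---|
| 15% | 10.3% | 0.923 / 0.947 | 1.03 | 1.08 |
| 20% | 13.9% | 0.896 / 0.929 | 1.04 | 1.11 |
| 30% | 21.3% | 0.841 / 0.890 | 1.06 | 1.16 |
| 40% | 29.0% | 0.783 / 0.847 | 1.08 | 1.22 |

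With equal mortality the ratio is 1.00.

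**Can the direction reverse?** The observed count ratio is the true rate ratio times the ratio of mean times alive.
- True rate ratio 0.95, mortality 20% on HFOT against 30% on LFOT: 0.95 × 0.896 / 0.841 = 1.01. A small benefit appears as none.
- True rate ratio 1.05, mortality 30% on HFOT against 20% on LFOT: 1.05 × 0.841 / 0.896 = 0.985. A small harm appears as a slight gain.
- True rate ratio 0.90, mortality 20% against 30%: 0.96. The direction holds, but the benefit is understated.

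A simulation at 1.5 events per year alive gave count ratios of 1.009 and 0.987 for the first two cases. Events per person-time gave 0.947 and 1.052, close to the true values.

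**The case against.** The strongest objection is that this belongs to the SAP. The article condenses a fuller protocol, promises a SAP before each secondary analysis, introduces its list as appropriate methods, and assigns no model by name to hospital days or ICU days. That is fair, and the SAP can still repair it. What remains is that the article does not stay silent: it publishes a list by outcome type, and that list does not fit several of its own outcomes. Followed as written, it leads to linear regression or a rank test.

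The other side is right to resist several stronger readings that a reader might infer:
- *That the plan has no method for unequal follow-up.* Cox and Fine–Gray both handle censoring for time-to-event outcomes. The gap concerns counts, days and rates only.
- *That every rate outcome is distorted.* A rate may already mean events per time at risk, in which case the shift does not arise. For these the point is only that no model is named.
- *That the 0.74 shows high mortality.* It is the proportion hospitalised or dead, and says nothing about death alone.
- *That these outcomes will point the wrong way.* Reversal needs a mortality gap that outweighs the effect while alive. Assuming 135 people per arm, a mean of 1.5 events and dispersion 1, the 95% limits on a rate ratio are about a factor of 0.73 to 1.36, because exp(±1.96 × √((2/135) × (1/1.5 + 1))) gives those values. A 6% shift lies well inside that.
- *That the cost analysis is biased.* Total days per randomised person, including days that come from living longer, are legitimate cost inputs.

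Mortality is also reported separately, and the composite rate counts death as an event. Both partly guard against misreading.

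**Conclusion.** The point holds in a limited form. For hospitalised days, ICU admissions, ICU days and number of exacerbations, the models named take no account of time at risk or over-dispersion; for the hospitalisation rates no model is named. If totals are compared directly, an arm with more early deaths looks better. The size is about 3% to 8% at 1 year under the assumed mortality range and hazard ratio, and about 8% to 22% at an assumed 3 years. It is nil if mortality is equal. All these figures rest on assumed mortality, constant hazards and equal event rates while alive, none of which the article supplies. The primary outcome includes death and is unaffected. This deserves correction before the secondary analyses but does not threaten the trial's main conclusion.

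**What to change.** In Statistical methods {20a}, and in the SAP, state that counts and rates are analysed by negative binomial regression with log time alive and at risk as offset, or by a recurrent-event model with robust variance and death as a terminal event. Add days alive and out of hospital to day 365, compared by a rank-based or bootstrap method, as the inferential analysis beside hospitalised days. Adding it is easier to defend than replacing a listed outcome while the trial is recruiting. Keep raw hospital and ICU days as descriptive results and cost inputs.

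The cost is wording and one added secondary analysis. The dates and stays needed already come from the patient, intensive care and cause-of-death registries, and the trial is not expected to finish before 2028. The offset alone has a limit: it removes the difference in exposure but not informative death, that is, sicker people both dying sooner and being admitted more often. The terminal-event model and days alive and out of hospital are there to address that.

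### Only Fine–Gray regression is named for secondary outcomes where death competes; a cause-specific hazard ratio should stand beside it

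*Protocol article*

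**What the plan says.** The protocol article, section 20a (statistical methods), divides the secondary time-to-event analyses in two: Cox models for ordinary survival outcomes, and "Fine–Gray regression for competing risk scenarios". No cause-specific hazard model is named for the second group, and nothing says that the effect on the competing event will be shown with each result. For the primary composite the same section says: "The primary outcome will be analysed using Cox proportional-hazards regression".

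Outcomes {12} lists several secondary outcomes that death can prevent:

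- exacerbation, whose definition does not include death: "Time to first exacerbation after randomisation, defined as time to first dispensed antibiotics and/or oral corticosteroids" (the definition continues with emergency visits and admissions; 1 year only);
- death from respiratory or from cardiovascular causes, where deaths from other causes compete;
- "Incidence of cardiovascular disease (at 1 year and long-term";
- "Need for home mechanical ventilation (at 1 year and long-term";
- stopping low-flow oxygen.

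All but exacerbation are listed both at 1 year and long-term. Only exacerbation is worded as a time to first event. The others fall under this point where they are analysed as time to event. All-cause mortality is itself a secondary outcome at both horizons. Details are deferred to an analysis plan that is not shown.

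**The concern.** Fine–Gray regression keeps people who have died from a competing cause in the risk set. Its hazard ratio therefore moves when treatment changes the event rate among the living, and also when treatment changes how many are alive to have the event. Objectives {7} asks for treatment effects on these other outcomes. A ratio above 1 for cardiovascular disease could mean that high-flow oxygen provokes it, or only that more people lived long enough to develop it. A ratio near 1 could hide a real reduction. The single number does not separate these readings, and the article names no second number that would. The Discussion describes the risk of hospitalisation and death in this population as very high, so competing death is not a marginal matter.

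**Working it through.** **What can be reproduced.** The article gives no figure on this point. Its sample size reproduces: 4 × 7.849 / (ln 0.67)² = 196 events, and 196 / 0.74 = 265, against the stated 270. The hazard ratio of 0.67 in that calculation belongs to the composite. Below it is borrowed as one assumed value for death.

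**Inputs, all assumed, since the article states no death rate.** Hazards are constant. The control death hazard is 0.40 per year (1-year risk without other events 1 − e^−0.40 = 0.33). The event hazard is 0.1 per year in both arms, so the true cause-specific hazard ratio is 1.00. The death hazard ratio is 0.67, giving 0.268 per year on high-flow oxygen. Allocation is 1:1, with administrative censoring only. The 3- and 5-year horizons are also assumed, because long-term is not defined.

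**Step 1: cumulative incidence.** With event hazard a and death hazard d, F(t) = a/(a+d) × (1 − e^−(a+d)t).

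- 1 year: control 0.2 × (1 − e^−0.5) = 0.079; high-flow 0.2717 × (1 − e^−0.368) = 0.084.
- 3 years: control 0.155; high-flow 0.182.
- 5 years: control 0.2 × (1 − e^−2.5) = 0.184; high-flow 0.2717 × (1 − e^−1.84) = 0.229.

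More people on high-flow oxygen have the event, although its rate among the living is the same in both arms.

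**Step 2: limiting Fine–Gray ratio.** Let f₀, f₁ be the event densities a·e^−(a+d)t and F₀, F₁ the cumulative incidences (0 = control, 1 = high-flow). The limit θ solves

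∫₀^τ { f₁ − (f₀ + f₁) · θ(1 − F₁) / [(1 − F₀) + θ(1 − F₁)] } dt = 0.

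| Death HR | 1 year | 3 years | 5 years |
|---|---|---|---|
| 0.67 | 1.065 | 1.18 | 1.26 |
| 1.00 | 1.00 | 1.00 | 1.00 |
| 1.5 | 0.91 | 0.80 | 0.74 |

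Hand check at 5 years for death HR 0.67: ln(1 − 0.229) / ln(1 − 0.184) = 1.28, close to 1.26. The cause-specific Cox ratio is 1.00 in every cell by construction. For a frequent event such as exacerbation (assumed 1.0 per year), the 1-year values are 1.07 and 0.91.

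**Step 3: sensitivity.** The ranges cover control mortality of 15–45% per year and event risk of 5–40% per year, again with no true effect on the event.

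| Death HR | 1 year | 3 years | 5 years |
|---|---|---|---|
| 0.67 | 1.03–1.10 | 1.08–1.25 | 1.12–1.35 |
| 0.80 | 1.02–1.06 | 1.05–1.14 | 1.07–1.19 |
| 1.25 | 0.94–0.98 | 0.86–0.95 | 0.83–0.93 |

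With 135 per arm and death HR 0.67, the chance of nominal significance for an untouched outcome is about 5–7% at 1 year, 6–21% at 3 years and 7–27% at 5 years.

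**Step 4: a masked benefit.** Take the step 1 inputs, but with a true cause-specific ratio of 0.85. The Fine–Gray ratio is then 0.91 at 1 year, 1.01 at 3 years and 1.08 at 5 years.

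**The case against.** The strongest reply is that nothing here is wrong. An effect on cumulative incidence is a legitimate target, and for the incidence of disease, the need for a ventilator or health-economic questions it may be the more useful one. The article does not define its target as the cause-specific hazard, does not map outcomes to models, and promises a detailed analysis plan that could add the second model. The cause-specific ratio is no neutral standard either. Reading it as the effect that would be seen without competing deaths requires those deaths to be unrelated to the outcome, which is doubtful in people this ill.

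Much of this stands. It rules out calling the Fine–Gray ratio biased, and it rules out replacing that ratio with the cause-specific one. It does not remove the point: the article does more than stay silent, since it assigns one model to this class of outcomes, and that model alone cannot separate the two effects.

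The size is also open to challenge. The death rate, the death hazard ratio and the long-term horizons are assumptions. The later figures need a mortality effect lasting for years, although high-flow oxygen after the trial is left to clinician and participant, and most pilot participants allocated to it stopped. For death from one cause, only deaths from other causes compete, so the full 0.40 per year overstates the shift.

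A reader might infer that a mortality harm would be disguised as benefit. The document does not support that: all-cause mortality is a planned outcome at 1 year and long-term, and death is part of the primary composite, so the harm would be open to view.

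**Conclusion.** The point holds as a modest improvement to the analysis of secondary outcomes. Fine–Gray regression gives a valid answer about cumulative incidence, but by itself it does not show whether high-flow oxygen changed the outcome or only survival. The shift is minor at 1 year: about 1.07 under the main assumptions and at most about 1.10 over the range examined for death HR 0.67. It becomes material at 3 to 5 years, about 1.18 to 1.26 under the main assumptions, and only if a mortality effect of that size persists. If mortality is unaffected, it is zero.

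A reader might also infer that a survival benefit would be reported as more exacerbations. That outcome is listed at 1 year only, where the shift is small, and the inference further requires that high-flow oxygen has no effect on exacerbations. The primary analysis is not affected, because death is part of its endpoint; nor is the sample size.

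**What to change.** State in section 20a, or in the analysis plan before database lock, that each secondary time-to-event outcome with competing death will be reported with three results: the cause-specific Cox hazard ratio with competing deaths censored, the Fine–Gray ratio, and cumulative-incidence curves by arm. Read these beside the mortality hazard ratio over the same horizon, using the all-cause mortality outcome already listed (for death from one cause, the ratio for deaths from other causes). Add that no claim of benefit or harm will rest on the subdistribution ratio alone. List the outcomes to which this applies, so that the choice is fixed before results are seen.

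The cost is one extra model per outcome on the same data and a second ratio to present and explain. The cause-specific ratio brings its own assumptions, which the report should state.

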## Data collection and management

### Plans for assessment and collection of outcomes {18a}

Outcome data will be obtained from patient questionnaires at baseline, 3 and 12 months, from Swedevox, from trial specific data entered in the eCRF by the PIs, and from national registries. In centres using the remote home-monitoring system AirView, data on HFOT utilisation will be used.

The questionnaires will include questions on oxygen and HFOT usage, patient preference for continuing the treatment, utilisation of primary care and domestic service, adverse events, and the number of exacerbations since the start of the trial. Symptoms included in the questionnaires are breathlessness using a modified Dyspnoea Exertion Scale (DES) [34] and the Dyspnoea-12 questionnaire [35, 36], cough and phlegm assessed by relevant items in the COPD Assessment Test (CAT) [37], sleep complaints using a modified Basic Nordic Sleep Questionnaire (BNSQ) [38], nasal symptoms, and subjective perception of change in health status assessed with a modified Global Impression of Change (GIC) scale [39]. Physical activity is reported for the previous month using a modified Grimby activity questionnaire [40, 41], and HRQL is evaluated using the CAT [37] and EuroQol Five Dimensions Five Levels (EQ5D-5D-5L) [42].

Data from Swedevox will be used for characterising the people and their oxygen treatment, and for assessment of rate and reason of LFOT withdrawal during follow-up. The ventilator arm of the Swedevox registry will be used to assess the incidence of long-term home mechanical ventilator usage.

If applicable, data on HFOT utilisation will be collected from centres using Airview at 1 week, 3 and 12 months on: average usage time, daytime and nighttime use, days of use, and days of use ≥ 4 h/24 h. Data on oxygen flow and HFOT settings will be collected from staff-reported questionnaires at 3 and 12 months.

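### The single covariate list for all outcome analyses omits the baseline score of HRQL and symptom outcomes, and the article does not say how the planned mixed models use that score

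*Protocol article*

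**What the plan says.** Section {20a} of the protocol article names a model for each type of outcome, including "linear regression for continuous outcomes, ensuring robust and context-appropriate analysis". For repeated measurements it adds: "Mixed regression models with random effects will be used to analyse outcomes measured in the same individual at several time points". The next sentence sets the covariates for all of these models together: "The outcome analyses will be adjusted for age and sex, the stratification variables, number of hospitalisations during the 12 months before baseline" and the time since LFOT was started in Swedevox. No outcome-specific exception follows.

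Section {18a} states: "Outcome data will be obtained from patient questionnaires at baseline, 3 and 12 months". The instruments include the modified DES, Dyspnoea-12, CAT items for cough and phlegm, and a modified BNSQ. For quality of life, "HRQL is evaluated using the CAT [37] and EuroQol Five Dimensions Five Levels". Section {12} lists the corresponding secondary outcomes at the two follow-up visits: "HRQL (at 3 and 12 months" and "Symptoms (dyspnea, cough, phlegm, upper airway symptoms, fatigue, including nighttime symptoms, sleep) (at 3 and 12 months".

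The article nowhere says whether a baseline score enters a model as a covariate, through a change score or as a repeated response. Section {20a} promises a detailed SAP before the database lock for the primary analysis and before each secondary analysis.

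**The concern.** The listed covariates suit a time-to-hospitalisation outcome. For a symptom or HRQL score, the same score at baseline is normally a useful predictor of the score at follow-up, and here it is already being collected. A model that follows the list literally, on the 3- and 12-month scores alone, leaves that information unused.

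Two things are at stake. The first is precision in outcomes for which no power is stated. The second is chance imbalance: if the arms happen to differ at baseline, part of that difference carries into the follow-up contrast. This matters most in the ILD cohort, which section {20b} analyses separately.

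Because the article names the covariates, an SAP that follows it literally would omit the baseline score. An SAP that adds the score would depart from the published list, in an open-label trial with patient-reported outcomes.

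**Working it through.** **Inputs from the article.** 270 people with COPD, 1:1 allocation, so 135 per arm; 40 with ILD, so about 20 per arm; hazard ratio 0.67, 80% power, two-sided alpha 0.05, 1-year event rate 0.74.

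**Assumed.** The correlation ρ between baseline and follow-up score is not in the article; 0.3, 0.5 and 0.7 are used. Scores are in SD units, with full response and no credit to the listed covariates.

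**The plan's own figure.** Reading 0.74 as the event proportion over both arms:
- Schoenfeld: 4(1.96 + 0.842)² / (ln 0.67)² = 196 events; 196 / 0.74 = 265 people.
- Freedman: (1.67 / 0.33)² × (1.96 + 0.842)² = 202 events; 202 / 0.74 = 273 people.
- 270 × 0.74 = 199.8 events give power 0.81 (Schoenfeld).

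The stated 270 is reproduced. It concerns only the time-to-event outcome and does not depend on this point.

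**Precision at one visit, COPD.** Without the baseline score, SE = √(2/n) = √(2/135) = 0.122 SD. With it as a covariate, SE = √(2(1 − ρ²)/n). The power row takes the difference that has 80% power unadjusted, (1.96 + 0.842) × 0.122 = 0.341 SD.

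| | ρ = 0.3 | ρ = 0.5 | ρ = 0.7 |
|---|---|---|---|
| Variance ratio 1 − ρ² | 0.91 | 0.75 | 0.51 |
| Adjusted SE (SD units) | 0.116 | 0.105 | 0.087 |
| Fall in SE, 1 − √(1 − ρ²) | 5% | 13% | 29% |
| Power for a 0.341 SD difference | 83.6% | 89.9% | 97.5% |
| Equivalent unadjusted N, 270/(1 − ρ²) | 297 | 360 | 529 |

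The percentage falls in variance and SE do not depend on n, so they also hold with fewer respondents.

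**Mean of the two visits.** With equal correlation between all visits, the variance factor is (1 + ρ)/2 unadjusted and (1 + ρ)/2 − ρ² adjusted. The ratios are 0.86 / 0.67 / 0.42, a fall of 14% / 33% / 58%.

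**Chance imbalance.** The difference in baseline means between arms has SD √(2/135) = 0.122 in COPD (95% range ±0.24) and √(2/20) = 0.316 in ILD (95% range ±0.62). Without adjustment, a fraction ρ carries into the follow-up contrast. A one-SD imbalance moves the COPD estimate by 0.04 / 0.06 / 0.09 SD and the ILD estimate by 0.316ρ = 0.09 / 0.16 / 0.22 SD.

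**What the mixed model would do.** SE of the 12-month contrast with 135 per arm and equal correlation between visits:

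| Use of baseline | ρ = 0.3 | ρ = 0.5 | ρ = 0.7 |
|---|---|---|---|
| Not used (3 and 12 months only) | 0.122 | 0.122 | 0.122 |
| Covariate | 0.116 | 0.105 | 0.087 |
| Response, common baseline mean | 0.116 | 0.105 | 0.087 |
| Response, arm means free at baseline (change contrast) | 0.144 | 0.122 | 0.094 |

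A further variant puts baseline in as a response row but fits only one constant group effect. With equal correlations the three visits get equal weight, so a true effect of (0, 1, 1) is estimated as (0 + 1 + 1)/3 = 2/3 of its size. Section {20a} as worded is compatible with every row of this table and with this variant.

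**The case against.** The strongest reply is that the plan may already use the baseline score. Section {18a} counts the baseline questionnaire as outcome data, and section {20a} assigns mixed models to outcomes measured repeatedly. Read together, baseline could be one of the repeated responses, and it would then not appear in a covariate list. With a common baseline mean, this recovers the whole gain. The reply stands as a possibility. It does not settle the matter, because the article does not choose that model and other models that fit its words lose precision or dilute the effect.

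A second reply is that such detail belongs in the SAP, and that the covariate sentence does not say these variables are the only ones. Both remarks are fair, and the SAP may resolve the point. But the article does not leave covariates to the SAP. It names them for all outcome analyses, so the choice is worth correcting where it is stated.

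A reader might also infer more than the document supports:
- **Systematic bias.** Randomisation keeps the unadjusted estimate unbiased on average. The loss is in precision and in exposure to chance imbalance.
- **Key outcomes in a sample with high attrition.** Section {12} does not rank its secondary outcomes, and no questionnaire attrition rate is given. The non-adherence reported in the Discussion concerns the device, and stopping treatment is not withdrawal.
- **Listed covariates that explain little of a symptom score.** The article has no figure on this. Whatever they do explain reduces the gains shown.
- **A large gain as a certainty.** At a correlation of 0.3 the SE falls by only about 5%.

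The schedule of assessments is a figure that is not shown, so which instruments are completed at baseline cannot be confirmed one by one.

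**Conclusion.** The point holds as one of precision and clarity in secondary outcomes. The stated adjustment set omits the baseline score, the baseline questionnaire is collected, and nothing in the article says that the score enters a model.

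If the list is followed with only the 3- and 12-month scores, the single-visit variance that could have been removed is at most about 9% / 25% / 49% at assumed correlations of 0.3 / 0.5 / 0.7, and the SE could have been about 5% / 13% / 29% smaller. These are upper values for each correlation. The loss disappears if the mixed model carries baseline as a response with a common mean. Exposure to chance imbalance is greatest in ILD, which the article itself calls exploratory. The primary analysis and the target of 270 are untouched.

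**What to change.** Add one sentence to section {20a}, and carry it into the SAP before database lock:

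*For each questionnaire outcome measured at baseline, the baseline value is included as a covariate in addition to the listed variables, or as a response with a common baseline mean across arms in a mixed model with treatment-by-visit effects at 3 and 12 months. Items without a baseline value, such as global impression of change, are excluded from this rule.*

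The SAP should name one of the two forms for each outcome. The cost is this sentence: no new data are needed, and the multiple imputation that section {20c} plans for missing predictors would cover missing baseline scores used as covariates.
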